### Interpreting instances of missing data

For missing data, we will apply multiple imputation methods to generate plausible values for missing observations under the assumption that data is missing at random. Sensitivity analyses are conducted to assess the impact of missing data by comparing results using different methods for handling missing data (e.g., Last Observation Carried Forward and multiple imputation). All statistical analyses are conducted using SPSS (version 25.0 or higher) or R software. Interim analyses will be used to recalculate the sample size.

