**Methods:**

This multicenter, randomized, double-blind, non-inferiority trial will enroll 228 patients with confirmed lumbar disc herniation and radicular pain. Participants will be randomly assigned (1:1) to receive an image-guided epidural injection of either DEP or compound betamethasone via interlaminar or transforaminal approach. Follow-up assessments will occur at 1 day, 1 week, 2 weeks, 4 weeks, 8 weeks, and 12 weeks post-injection. The primary outcome is leg pain intensity at 4 weeks, measured by the numeric rating scale (NRS). Secondary outcomes include NRS at other time points, functional disability (ODI and RMDQ), mental health (GAD-7 and PHQ-9), morning serum cortisol, patient satisfaction, and adverse events. A second injection may be administered at 4 weeks based on clinical response.

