### Study sample size

Assuming there is no difference in the mean NRS score between groups at 4 weeks after treatment, with a standard deviation of 2.2, a two-sided α of 0.05 (equivalent to a one-sided α of 0.025), and a power (1–β) of 0.90, and setting a non-inferiority margin of 1 (less than the minimal clinically important difference of 1.5), a 1:1 allocation ratio between the experimental and control groups was used. Based on PASS software calculations, 102 participants per group were required. After accounting for an estimated 10% loss to follow-up and refusal rate, the final required sample size was determined to be 114 participants per group (Feeley et al., 2017).

A non-inferiority margin of one point on the NRS was selected based on the established minimal clinically important difference (MCID) for radicular pain. This margin was chosen to balance statistical rigor with clinical relevance, allowing detection of whether dexamethasone palmitate maintains acceptable analgesic efficacy compared with standard corticosteroid therapy. From a clinical perspective, demonstrating non-inferiority would support the use of dexamethasone palmitate as a viable alternative treatment option, particularly if it offers additional pharmacological advantages such as prolonged tissue retention or improved safety characteristics.

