### Criteria for trial discontinuation

Participation in the trial may be discontinued under the following conditions:Occurrence of any serious adverse event related to the study intervention;Significant worsening of symptoms, including increased pain intensity or new or progressive neurological deficits (e.g., motor weakness, sensory loss);Development of procedure-related complications (e.g., infection, bleeding, or suspected vascular injury);Any unexpected clinical condition that, in the judgment of the primary investigator, makes continued participation unsafe;Withdrawal of consent by the participant at any time.

All discontinuation events will be documented, including the reason and timing, to ensure transparency in data analysis.

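### The named missing-data checks (LOCF against MAR multiple imputation) do not test departures from MAR, although patients may leave because of increased pain

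*Protocol article*

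**What the plan says.** The primary endpoint is leg pain at week 4: "The primary outcome is leg pain intensity at 4 weeks, measured by the numeric rating scale (NRS"). Under Primary outcome analysis it is analysed with a linear mixed-effects model. Non-inferiority is concluded if the upper limit of the two-sided 95% interval for the difference is no more than 1 point, and both intention-to-treat and per-protocol analyses are run.

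Under Interpreting instances of missing data, values are multiply imputed "under the assumption that data is missing at random". Sensitivity is then judged by comparing "different methods for handling missing data (e.g., Last Observation Carried Forward and multiple imputation").

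Under Criteria for trial discontinuation, one ground for ending participation is "Significant worsening of symptoms, including increased pain intensity". The section requires the reason and timing of each exit to be documented. It does not say whether pain scores are still collected afterwards. The visits before week 4 are day 1, week 1 and week 2 (Table 1).

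**The concern.** The two parts of the plan do not fit together. The discontinuation criteria create a route by which a week-4 score can be missing because it would have been high. The sensitivity analysis should therefore ask what happens if the missing scores are worse than the observed data predict. One of the two named methods repeats the main MAR method. The other, LOCF, assumes that pain stays at its last recorded value, so any loss of effect between that visit and week 4 disappears.

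In a non-inferiority trial, an error that draws the arms together makes the claim easier to reach. The Discussion accepts that particulate steroids may hold a modest advantage in duration, so a late fading of DEP is a possibility the protocol itself raises. If it happened and the affected patients left unseen, both methods could miss it, and their agreement would be reported as robustness.

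**Working it through.** **Inputs from the Protocol article (Study sample size).** "with a standard deviation of 2.2"; "a two-sided α of 0.05 (equivalent to a one-sided α of 0.025"); "a power (1–β) of 0.90"; margin 1; true difference 0; 102 evaluable per group; 10% loss; 114 enrolled per group.

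**Step 1: the plan's own figure.** n = 2 × 2.2² × (1.960 + 1.282)² / 1² = 101.7, rounded up to 102. Inflated for loss: 102 / 0.90 = 113.3, rounded up to 114. Both figures reproduce.

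**Step 2: what an undetected bias does at the margin.** If the true difference is 1 and the estimate is biased by b towards equality, the one-sided error is about Φ(b/SE − 1.96). SE is 2.2 × √(2/102) = 0.308 with 102 per arm, and 2.2 × √(2/114) = 0.291 with 114.

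| Bias b | Error, 102 per arm | Error, 114 per arm |
|---|---|---|
| 0 | 2.5% | 2.5% |
| 0.1 | 5.1% | 5.3% |
| 0.2 | 9.5% | 10.1% |
| 0.3 | 16.2% | 17.6% |

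**Step 3: can LOCF and MAR agree and both be wrong?** This was simulated with 3,000 trials per scenario and 114 per arm. The following are assumptions, not document figures:
- Between-patient SD 1.7 and residual SD 1.4, so total SD √(1.7² + 1.4²) = 2.2.
- DEP deficit of 0, 0.3, 0.6 and 1.0 at day 1, week 1, week 2 and week 4.
- Exit between week 2 and week 4, with a probability that rises with the pain score (scenario c: control arm only, random on DEP).
- LOCF carries the week-2 score. MAR imputation is a within-arm regression on the three earlier scores.

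| Scenario | Missing, DEP vs control | Full data | LOCF | MAR |
|---|---|---|---|---|
| (a) Exit depends on the unseen week-4 score | 17% vs 9% | 1.00 | 0.86 | 0.86 |
| (b) Exit depends on the recorded week-2 score | 16% vs 12% | 0.99 | 0.97 | 0.99 |
| (c) Outcome-related exit in control only; random on DEP | 10% vs 17% | 1.01 | 1.15 | 1.34 |

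In (a) the two methods agree and both favour non-inferiority by about 0.14. By the step 2 formula that is an error near 7%: Φ(0.14/0.308 − 1.96) = Φ(−1.51). In (b) there is almost no bias. In (c) the bias runs against non-inferiority.

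**Step 4: what a delta adjustment would show.** With 10% missing in the DEP arm, adding D points to the imputed DEP scores moves the estimate by 0.10 × D. With 102 observed per arm the half-width is 1.96 × 0.308 = 0.604, so non-inferiority needs an estimate of at most 1 − 0.604 = 0.396. The tipping shift is (0.396 − observed difference) / 0.10:
- observed difference 0: 3.96 points
- observed difference 0.2: 1.96 points
- observed difference 0.3: 0.96 points

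This holds the SE fixed and so ignores the extra variance from imputation.

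**The case against.** Four objections carry weight.

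**The list is open.** The two methods are given as examples, and an analysis plan that is not shown may add others. A reader might infer that missing data will be checked by these methods only; the text does not support that. What stands is that the methods the protocol chose to name do not probe the assumption most open to doubt, and that LOCF is a weak choice to name.

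**The direction is not fixed.** A reader might infer that the planned check always leans towards non-inferiority. Scenarios (b) and (c) show otherwise. Imputation uses the day-1, week-1 and week-2 scores, discontinuation for worsening is permitted rather than required, and LOCF would itself carry forward a worsened score once recorded. The Discussion also credits DEP with a prolonged action, so late fading is a possibility and not an expectation.

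**The sizes rest on assumptions.** The documents give one dropout figure, 10% loss, with no split by arm, exit probability or pain trajectory. Scenario (a) has 17% missing on DEP, above the planned rate. The error rates in step 2 are conditional on a bias of the stated size and do not forecast this trial's error.

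**LOCF does not decide the trial.** It is named only for sensitivity, so an inflated LOCF error rate is not the trial's type I error. The harm is narrower: false reassurance about the primary result.

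Two possible replies do not remove the point. Documenting the reasons for exit describes dropout without adjusting for it, and running both intention-to-treat and per-protocol analyses does not recover a score lost because it was high.

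**Conclusion.** The concern holds in a limited form. The named comparison sets MAR imputation against LOCF and tests no departure from MAR, while the plan permits exit for increased pain. Agreement between the two is therefore weak evidence of robustness: under hidden DEP failures both can be biased towards non-inferiority by a similar amount (0.14 in scenario (a)). A bias of 0.1, 0.2 or 0.3 would take the one-sided error at the margin from 2.5% to about 5%, 10% or 16–18%. Whether such a bias arises, and in which direction, depends on an exit pattern the data cannot reveal. That uncertainty is the reason for a check outside MAR; it does not show that the trial is biased. This is an inexpensive improvement to the stated method, and the primary analysis and sample size are unaffected.

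**What to change.** Keep the MAR analysis as primary. Replace LOCF with one prespecified delta-adjusted multiple imputation that adds a penalty to imputed week-4 scores in the DEP arm over a stated range. Report the tipping point at which the upper 95% limit reaches 1, and judge whether a shift of that size is plausible given the recorded exit reasons. A fixed pass threshold is not needed: requiring survival of a 1-point penalty, for example, would cut the chance of passing for truly equal drugs from about 90% to about 83% (Φ((1 − 0.1)/0.308 − 1.96)).

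Also state that the week-4 pain score is still collected after discontinuation unless consent is withdrawn. This reduces the problem at its source.

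The analysis change costs a paragraph of text and a few lines of code, and should be fixed before unblinding because penalties chosen later carry little weight. Continued collection adds some follow-up effort for patients who discontinue. The downside is that robustness becomes harder to claim: the tipping shift is about 4.0 points at an observed difference of 0, but only about 2.0 at 0.2 and about 1.0 at 0.3.

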### Data and safety monitoring

In this trial, adverse events (AEs) and unintended effects related to the intervention or trial conduct are systematically recorded and managed following a standardized protocol. All solicited AEs are actively monitored, and participants are asked about specific symptoms immediately after the injection, at each scheduled follow-up visit, and via telephone contact during the follow-up period. Any spontaneously reported AEs are documented whenever they occur.

Trained site personnel assess the severity, causality, and duration of each event, and record these details in the case report form. Serious adverse events (SAEs), defined as any unintended medical occurrence resulting in death, being life-threatening, requiring hospitalization or prolongation of hospitalization, or resulting in persistent or significant disability/incapacity, are reported immediately to the principal investigator and the ethics committee.

All AEs, regardless of suspected causality, are included in the final analysis to ensure a comprehensive safety evaluation of dexamethasone palmitate and betamethasone in the treatment of lumbar disc herniation.

A formal independent Data and Safety Monitoring Board (DSMB) was not established in this study due to the routine clinical nature and relatively low-risk profile of epidural steroid injections. However, safety oversight is ensured through continuous monitoring by the principal investigator and periodic review by the institutional ethics committee.

Data management is performed by trained personnel at each participating center. Double data entry is used to minimize transcription errors, with two independent entries for each record. Range and consistency checks are implemented to identify outliers or data entry errors. Regular data audits are conducted to ensure completeness, accuracy, and protocol adherence.

## Discussion

This protocol outlines a multicenter, randomized, double-blind non-inferiority trial comparing dexamethasone palmitate (DEP) with compound betamethasone for epidural injection in patients experiencing lumbar radicular pain. The study is designed to evaluate whether DEP, a novel lipophilic corticosteroid, can achieve similar clinical outcomes to a widely used particulate steroid, while potentially reducing safety concerns and improving pharmacokinetic properties.

Lumbar nerve root compression due to intervertebral disc displacement is a frequent cause of lower limb pain and functional impairment (Deyo and Mirza, 2016). Epidural steroid administration is a common interventional approach, but current evidence does not clarify the optimal choice of corticosteroid (Kreiner et al., 2014; Figueiredo et al., 2020). Particulate agents, such as betamethasone, may offer longer-lasting relief, but carry risks associated with crystal formation.

Dexamethasone palmitate (DEP) is as a prodrug of dexamethasone, consisting of dexamethasone combined with a fat emulsion that includes lecithin (Harasim-Symbor et al., 2016). Compared to dexamethasone, DEP is more readily taken up by activated macrophages due to its fat emulsion properties, which ensures robust distribution in inflammatory tissues while minimizing the risk of adverse effects (Li et al., 2024). Other benefits include a prolonged duration of action due to DEP’s liposome structure. And when mixed with local anesthetics, does not produce significant particulate formation (Hui et al., 2023).

The primary endpoint, leg pain intensity at 4 weeks post-injection, reflects both short-term and early sustained analgesic effects. Secondary endpoints include functional improvement and safety outcomes, including adverse event incidence and serum cortisol levels. A non-inferiority framework was chosen to determine whether DEP can provide outcomes that are clinically comparable to standard particulate therapy, recognizing that particulate agents may have a modest advantage in analgesic duration.

Patient safety remains a priority. Epidural injections carry procedure-specific hazards, such as transient neurological symptoms, inadvertent vascular injection, and infection (Kozlov et al., 2015). All procedures will be conducted under imaging guidance, following standardized techniques. Consent is obtained by trained personnel, who provide detailed information on potential benefits and procedure-related risks. Serious adverse events are promptly reported to investigators and the ethics committee, ensuring close oversight.

Potential sources of variability include the choice of injection route and local anesthetic concentration. Prior research and guideline recommendations suggest these factors minimally affect efficacy, and they will be addressed in the statistical analysis through subgroup evaluation. Multicenter coordination, standardized training, and stratified randomization by baseline characteristics are implemented to maintain consistency across sites.

Several limitations should be acknowledged in this study. First, this trial does not include a comparison with water-soluble dexamethasone, which may be more commonly used in high-risk epidural injections; such a comparison would provide additional clinically relevant information on the relative efficacy and safety of different non-particulate corticosteroids. Second, the study allows variability in injection technique (interlaminar vs. transforaminal) and local anesthetic concentration, reflecting real-world clinical practice where individual physician preferences differ. While this may introduce heterogeneity, it enhances the external validity and generalizability of the findings to routine clinical settings. Third, as a multicenter trial, differences in operator experience, procedural nuances, and patient management across sites may affect consistency, although standardized protocols, training, and stratified randomization by baseline severity are implemented to mitigate these influences. Last, the absence of assessment for pain catastrophizing, such as the Pain Catastrophizing Scale (PCS). Psychological factors like catastrophizing may influence pain perception and treatment response, and their omission may limit the ability to fully account for these potential confounders.

## Conclusion

This study protocol describes a randomized, double-blind, non-inferiority trial designed to evaluate the efficacy and safety of dexamethasone palmitate compared with compound betamethasone for lumbar radiculopathy. By addressing an important gap in evidence regarding the use of dexamethasone palmitate in epidural injection therapy, this study may provide clinically relevant data to guide the selection of corticosteroid formulations in routine practice. The findings are expected to support informed clinical decision-making, optimize therapeutic strategies, and provide a foundation for future studies on alternative steroid options for lumbar radicular pain.
